# Developing and testing tele-support psychotherapy using mobile phones for depression among youth in Kampala district, Uganda: study protocol for a pilot randomized controlled trial

**DOI:** 10.3389/fdgth.2025.1515193

**Published:** 2025-02-18

**Keywords:** tele-support psychotherapy, depression, COVID-19, youth, Uganda tele-support psychotherapy, randomized controlled trial, Uganda

## Abstract

**Introduction:**

In the post-COVID-19 era, depressive disorders among youth have risen significantly, creating an urgent need for accessible, cost-effective mental health interventions. This study adapts Group Support Psychotherapy into Tele-Support Psychotherapy (TSP) via mobile phones. It aims to evaluate its feasibility, acceptability, effectiveness, and cost-efficiency in addressing mild to moderate depression among youth in central Uganda.

**Methods and analysis:**

This study will use a mixed-methods approach, starting with a qualitative phase to adapt Group Support Psychotherapy into Tele-Support Psychotherapy (TSP) via mobile phones. Guided by ecological theories and the Unified Theory of Acceptance and Use of Technology (UTAUT), focus group discussions and interviews with youth, mental health professionals, and stakeholders will inform the development of a youth-tailored call platform integrated into Rocket Health Africa's telehealth services. Data will be analyzed using grounded theory and MAXQDA Analytics Pro 2022 to guide intervention adaptation. An open-label randomized controlled trial will enroll 300 youth (15–30 years) with mild to moderate depression from Kampala, Uganda, to evaluate Tele-Support Psychotherapy (TSP). Participants will be randomized to TSP with standard mental health services (SMHS) or SMHS alone. Primary outcomes include feasibility and acceptability, with secondary outcomes assessing cost-effectiveness, depressive symptom changes, and social support. Intention-to-treat analysis using structural equation modeling will evaluate treatment effects, complemented by qualitative insights into implementation barriers and facilitators.

**Discussion:**

This study protocol develops and evaluates Tele-Support Psychotherapy (TSP) for youth depression in resource-limited settings, addressing mental health gaps exacerbated by COVID-19. Using user-centered design and mixed methods, it explores TSP's feasibility, adaptability, and cost-effectiveness while addressing barriers like technology literacy, laying the groundwork for accessible digital mental health solutions.

**Trial Registration:**

PACTR202201684613316.

## Introduction

There is growing recognition of tele-psychotherapy as a viable and effective treatment for depression among youth, offering a convenient and accessible option for mental health care (1). This approach is crucial in addressing the increasing mental health issues, such as depression and associated stigma (2). Notably, many mental health problems are mild to moderate in severity and respond well to first-line psychological treatments (3).

Depression among youth in Kampala, particularly in vulnerable populations, is a critical concern exacerbated by socio-economic challenges, violence, and inadequate healthcare access, with young women disproportionately affected. A systematic review and meta-analysis found that the pooled prevalence of depression in Uganda is approximately 30.2%, with refugees experiencing the highest rates at 67.63% (4, 5). Experiences of sexual and physical violence, along with the SAVA syndemic (substance use, violence, and HIV/AIDS), further increase vulnerability to depression (6, 7). The lack of adequate healthcare access is a significant barrier to addressing mental health issues among these groups.

The Covid-19 pandemic has highlighted the need for telemedicine in low- and middle-income countries (LMICs), which face unique challenges due to strained healthcare systems and limited resources. Despite technological, regulatory, and economic challenges, there has been a high level of acceptance for telemedicine services in these regions during the pandemic (8) While online therapeutic services have been around long before the dawn of the COVID-19 pandemic in high-income countries (HICs), they were limited in low- and middle-income countries (9). Most mental health professionals in LMICs had to transition towards tele- psychotherapy for the first time to provide ongoing care (10). This new treatment modality makes it necessary for researchers in LMICs to start investigating and documenting the processes involved in delivering tele-psychotherapy and the treatment outcomes.

Digital mental health interventions for youth are emerging in sub-Saharan Africa. For instance, interventions like “Shamiri Digital” and “Kuamsha” have shown promise in reducing depressive symptoms, with “Shamiri Digital” demonstrating significant improvements through growth mindset, gratitude, and value affirmation techniques (11), and “Kuamsha” using a gamified, user-centred design for behavioural activation therapy (12). However, limited research in low-resource settings and the lack of standardized, culturally sensitive approaches emphasise the need for further rigorous evaluations and adaptations (13). A scoping review of 64 studies describing 57 mental health interventions for adolescents in sub-Saharan Africa revealed a significant gap in the use of digital mental health interventions (14). This underutilization highlights an opportunity for further research and development to assess the feasibility and effectiveness of incorporating digital technologies. Leveraging these tools could enhance mental health support for some adolescents in the region.

Digital health interventions (DHIs) in sub-Saharan Africa have shown promise in improving health outcomes across various domains, though effectiveness varies due to systemic challenges like lack of coordination, scalability, and infrastructure deficits (15, 16). For HIV care, telemedicine has improved palliative care communication, while ART adherence interventions show mixed results, with some success using SMS reminders (17, 18). mHealth interventions have facilitated care for NCDs, though their success depends on patient attitudes and resources (19). Similarly, mobile interventions have improved maternal health services in underserved areas but require better evaluation (20).

Tele-psychotherapy has proven to be an effective and accessible alternative to traditional in-person therapy for managing anxiety and depression, utilizing modalities such as telephone, video, and online platforms. Studies highlight the benefits of telephone-administered psychotherapy in reducing depression severity with high adherence rates (21) and mobile phone support in improving depression management outcomes (22). Computerized cognitive behavioral therapy (cCBT) has also shown effectiveness in reducing anxiety and depression symptoms, particularly with supervision to improve adherence and reduce dropout rates (23, 24). Young people in developing countries prefer interactive, game-like digital interventions with personalized and social features (25, 26), though low engagement and technical issues remain challenges. Co-designing these platforms with young people and caregivers enhances their acceptability and effectiveness, ensuring they meet user needs and preferences (27, 28).

Previously, we developed culturally appropriate group support psychotherapy to treat mild to moderate depression (29). Our comprehensive research demonstrated that these approaches effectively address depression and enhance physical health and can be administered by lay health workers, alleviating the critical shortage of mental health professionals available to provide services to those in need (30, 31). In this context, we collaborated with the Medical Concierge Group (TMCG) to transform group support psychotherapy (GSP) into tele-support psychotherapy (TSP), which is offered individually through mobile phones. TMCG, a prominent digital health enterprise in Uganda, has demonstrated the practicality, acceptance, and effects of tele-health in diverse medical fields. However, their offerings currently lack tele-psychotherapy (32). The specifics of setting up tele-psychotherapy and the results from such services remain largely unexplored.

The Unified Theory of Acceptance and Use of Technology (UTAUT) is a widely used framework for understanding the factors influencing technology adoption, focusing on performance expectancy, effort expectancy, social influence, and facilitating conditions as key determinants (33). Extensions of the model incorporate factors like trust, perceived enjoyment, and satisfaction, highlighting the need for context-specific adaptations to address variations in demographic and educational contexts (34, 35). Performance expectancy and ease of use consistently emerge as critical predictors of behavioural intention, while social influence and facilitating conditions play variable roles depending on the context (36, 37). The UTAUT model will be used to guide the development and evaluation of tele-support psychotherapy, as it identifies the factors influencing user acceptance of digital mental health interventions. By addressing these determinants, such as ensuring ease of use, cultural relevance, and accessible resources, the model will enhance the design and scalability of tele-support psychotherapy, ensuring it meets the needs and preferences of target populations, particularly youth.

Further, the Ecological Validity and Culturally Sensitive Framework is crucial in designing tele-psychotherapy interventions, especially in diverse cultural settings. This framework will ensure that TSP is tailored to the cultural and environmental contexts of the target population. This approach will not only respect the cultural nuances of the population but also increase the likelihood of successful implementation and acceptance of the intervention.

This paper outlines the protocol for development and evaluation of Tele-Support Psychotherapy (TSP, administered by lay counselors) using mobile phones, for treating mild to moderate depression among Ugandan youth. In the initial phase, we will conduct community-based participatory qualitative research to gather insights for developing a call platform and adapting Group Support Psychotherapy (GSP) into a Tele-Support Psychotherapy (TSP) model tailored for youth depression treatment. In the trial phase, the primary objective will be to evaluate the feasibility, and acceptability of TSP delivered via mobile phones by lay counsellors as a treatment for mild to moderate depression among youth in the Kampala district.

Further, we will determine whether TSP using mobile phones can be delivered by lay counselors as planned and also explore causal and contextual factors (barriers and facilitators) influencing access to TSP. Secondary objectives will include an exploration of the preliminary effectiveness and cost-effectiveness of tele-support psychotherapy using mobile phones in treating mild to moderate depression among youth. Further, we will explore mediators and moderators of the effect of TSP on depression. We hypothesize that compared to the control intervention, TSP using mobile phones will demonstrate better feasibility, acceptability, preliminary effectiveness, and cost-effectiveness. The primary endpoint will be six months from baseline. The data obtained will be used to design a definitive trial which will test the hypothesis that TSP added to SMHS leads to more reduction in depression symptoms than the sole use of SMHS among youth in Kampala district.

## Methods

### Study setting

The study will take place in three distinct areas within the Kampala district: the slums of Naguru Go-down and Kamwokya, and the student community at Makerere University. Kampala has 62 slums, accommodating half of the city's population on just 16% of its land. Kamwokya stands out as one of the most notorious slums, known for its high density, housing around 6,380 people, and grappling with inadequate infrastructure and significant public health issues. Naguru Go-down, located in central Kampala, comprises roughly 2,080 households, totalling an estimated population of 10,400, with an average household size of five individuals. Makerere University, Uganda's largest public university, hosts around 35,000 students aged 18–30. These communities, drawing youth from across the nation, are characterized by their diversity and high density, making them particularly susceptible to a range of public health challenges, including poverty, underemployment, financial and academic pressures, drug use, and overcrowding (38).

### Study design

During the preparatory phase, a qualitative study will be carried out. Co-principal investigator [name], leveraging over ten years of connections with officials and health centers in the Kampala district, will facilitate introductions between the research team and important local figures. We plan to hold nine focus group discussions (FGDs) with youth, community health workers, and political representatives from the three target areas: Naguru, Kamwokya, and Makerere, each hosting 3 discussions. Additionally, key informant interviews (KIs) with a diverse group of 10 stakeholders, including psychologists, health officials, community and religious leaders, will explore their understanding, perspectives, and attitudes towards employing tele-psychotherapy for youth mental health issues. For the qualitative interviews, we will employ purposive sampling, conducting them in the local dialect. These interviews will be audio-recorded, then transcribed and, where necessary, translated word-for-word. Prior to the KIs and FGDs, informed consent will be secured from all participants.

In conjunction with these efforts, we will establish a Community Advisory Board (CAB) that includes diverse community representatives such as a community and youth leader, a faith healer, local council and student leaders, a community health worker, and a representative from key populations. The CAB's role is to ensure ongoing trust in the research activities within the community. CAB members will also be involved in the KIs, enhancing the research's credibility and providing essential feedback on the TSP model and study protocol, especially regarding mental health and psychosocial issues. Insights from these interviews and discussions will inform adjustments to the GSP content, making it suitable for TSP delivery to youth through mobile technology.

Collaboration will be sought with professional counsellors (*N* = 10) who will receive training in the delivery of TSP. Training workshops will also be used to review our theoretical framework and select psychotherapeutic skills from the GSP model to be used in the TSP model for youth. Further, we will refine lay health workers’ training materials and guides. These professionals will train, mentor and supervise 40 lay counsellors who will deliver tele-psychotherapy through a virtual platform to youth with mild to moderate depression.

In the trial phase, we shall conduct a pilot single-blinded randomized controlled trial to test the feasibility and

acceptability of using TSP in combination with standard mental health services(SMHS) vs. SMHS only to treat mild to moderate depression among youth in Kampala district. We aim to randomize 300 youth (1:1) to either both TSP and SMHS (*N* = 150) or SMHS only (*N* = 150). The 150 subjects in each arm will be recruited from three communities (Makerere University (*N* = 50), Kamwokya slums (*N* = 50) and Naguru go-down slums (*N* = 50) in each treatment arm and invited to participate. Participants will be evaluated at baseline, 6 and 12 months after baseline assessment.

A longitudinal process evaluation of the delivery of TSP using mobile phones and SMHS using mixed methods will run alongside the trial to assess acceptability, feasibility, fidelity, barriers and facilitators and how intervention recipients respond to the different intervention components. Open-ended exit interviews with recruited trained lay counsellors and study participants will seek to understand stressors in their communities, their own psychosocial support needs, and their knowledge regarding mental health after training, satisfaction, barriers and facilitators of participation in TSP sessions. Attendance registers and training logs will be used to track indicators of feasibility.

The study protocol is registered in the Pan African Clinical Trials Registry. The reporting of the trial will be in accordance with the Standard Protocol Items: Recommendations for Interventional Trials (SPIRIT) guidelines (39) for intervention trials (see Supplementary File S1) and the CONSORT statements for pilot randomized trials (40). The study was submitted to and approved by both the Makerere University College of Health Sciences Research Ethics Committee and the Uganda National Council of Science and Technology. All study participants will be required to provide written informed consent. Participants will receive a financial incentive to compensate for their time and defray internet data costs (if any). Figure 1 summarizes the trial profile.

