### The tele-psychotherapy call center

The tele-psychotherapy platform will be developed as an extension of The Medical Concierge Group (TMCG)'s existing tele-health services, also known as Rocket Health Africa. TMCG, a pioneering digital health entity, harnesses technology to offer a range of healthcare solutions including remote doctor consultations, community-based laboratory sample collection, doorstep pharmacy deliveries, and the creation of digital platforms for healthcare initiatives and research. For the prototype, the technical team will utilize detailed insights and schematic representations to craft the first version of the call platform. This will involve adapting the current infrastructure to introduce a mental health-specific toll-free line, ensuring community members can directly connect to the Rocket Health call center.

Upon dialing in, calls will be automatically redirected to available lay counselors, facilitating immediate start of the psychotherapy sessions. Following the initial setup, the developers will provide comprehensive orientation and training for the counselors involved in the project. These counselors, in turn, will educate their clients on navigating the call center access. Continuous enhancement of the call platform will be guided by user feedback, ensuring the service remains responsive to the needs of its clients.

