### Sample size estimation

In a pilot trial the objective is not to prove superiority of the treatment but to test trial procedures and processes and to get estimates of parameters for the main trial sample size. According to Sim and Lewis et al, 2012, they propose a rule of the thumb for sample size of a pilot study which states that the sample size should be ≥55 and they do not put an upper limit (41). Other researchers argue that there is a trade-off, therefore, between having a small pilot study and a larger main trial or a larger pilot study and a smaller main trial. This is because the larger the pilot the more precisely estimated the variance will be and, hence, the smaller the inflation factor applied to the main study sample size calculation (42). For these reasons, we increased the sample size to 150 in each treatment arm.

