We will assess randomization across the two arms by comparing socio-demographic characteristics and other potential confounding variables using chi-square for categorical variables and t-tests or other equivalent nonparametric tests, as appropriate, for continuous variables. Secondary outcomes will be the difference in follow-up mean depression, anxiety, stigma and social support scores between TSP-SMHS and SMHS (Control group) participants. These outcomes will be analyzed by ITT using generalized structural equation modelling. The STATA 16 statistical software will be used to conduct all analyses. Missing values will be imputed with multiple imputations.

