## Results

### Trial status

The Makerere School of Health Sciences Research Ethics Committee and the Uganda National Council of Science and Technology have granted approval for the trial. Recruitment commenced in May 2023 and concluded in July 2023, successfully enrolling 300 youths aged 15–30 years with mild to moderate depression levels. In parallel with the recruitment, TMCG developed the telepsychotherapy call platform. Those participants were randomly assigned to two groups: 154 were instructed to use their mobile phones to call the tele-psychotherapy platform to receive both Tele-support psychotherapy (TSP) and also to go to the nearest mental health treatment center for Standard Mental Health Services (SMHS) if their depression symptoms do not improve, and 146 were instructed to go to the nearest mental health treatment center and seek SMHS only. Currently, the analysis of data collected at the baseline is underway. The findings from this study are slated for presentation at both national and international forums. Efforts are also being made to draft manuscripts for submission to peer-reviewed academic journals, and comprehensive reports will be compiled for the funding body.

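### The stated between-arm model has no term for the 40 lay counsellors who deliver TSP in one arm only, and the pilot does not plan to report a counsellor ICC for the definitive trial

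*Protocol article*

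**What the plan says.** Under Study design, 10 professional counsellors are to "train, mentor and supervise 40 lay counsellors who will deliver tele-psychotherapy". The Introduction says that TSP is given individually by phone, and the control arm has no lay counsellors. The planned allocation is "We aim to randomize 300 youth (1:1) to either both TSP and SMHS" or SMHS alone, 150 per arm. Trial status reports the realised split: "154 were instructed to use their mobile phones to call the tele-psychotherapy platform", and 146 were sent to SMHS only.

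The call center section says that "calls will be automatically redirected to available lay counselors". It also speaks of counsellors teaching their own clients how to reach the service, and Retention has lay health workers phone participants who miss sessions. Whether a participant stays with one counsellor over the eight sessions is therefore not settled.

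On the between-arm comparisons of depression, anxiety, stigma and social support scores, which are secondary outcomes, Statistical analyses says: "These outcomes will be analyzed by ITT using generalized structural equation modelling". It adds the software and multiple imputation. It names no counsellor level, random effect or clustered variance.

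Sample size estimation says that one aim of the pilot is "to get estimates of parameters for the main trial sample size". The only parameter it goes on to discuss is the variance. The article nowhere mentions an intraclass correlation.

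**The concern.** Participants treated by the same counsellor may do similarly well or badly because of that counsellor's skill. The protocol itself treats the counsellor as relevant: it measures therapeutic alliance, and counsellor knowledge and attitudes. Because lay counsellors work in the TSP arm only, any such correlation adds variance to one side of the comparison (a partially clustered design). A model without a counsellor term leaves that variance out, so its intervals are too narrow.

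Two things are at stake. In the pilot, it is the honesty of the intervals around preliminary effect estimates. Beyond the pilot, it is the size of the definitive trial: the counsellor ICC is one of the parameters needed to size a trial of a counsellor-delivered therapy, and its effect grows with the number of clients each counsellor carries. The ICC can be estimated only if the link between participant and counsellor has been recorded.

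**Working it through.** **What can be reproduced.** The plan gives no power calculation, so there is no design figure to re-derive. The 150 per arm rests on a rule of thumb (at least 55) and a precision argument. The counts agree: 3 × 50 = 150 per arm, and 154 + 146 = 300.

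**Inputs from the documents.** TSP n = 154, control n = 146, counsellors = 40, sessions = 8. Mean caseload m = 154/40 = 3.85 (150/40 = 3.75 as planned).

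**Assumptions, not in the documents.** Counsellor ICC of 0.02, 0.05 or 0.10; caseload CV of 0 (even) or 0.8 (uneven); 10 clients per counsellor in a definitive trial.

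**Step 1: pilot, one counsellor per participant.**

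- Design effect in the TSP arm: DE = 1 + ((1 + CV²)m − 1) × ICC.
- SE ratio (true to unadjusted) = √[(DE/154 + 1/146) / (1/154 + 1/146)].
- True two-sided error of a nominal 5% test = 2(1 − Φ(1.96 / SE ratio)).

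Example, ICC 0.05 and CV 0: DE = 1 + 2.85 × 0.05 = 1.1425, and the SE ratio is 1.034.

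| ICC | DE, even | SE excess | Type I error | DE, CV 0.8 | SE excess | Type I error |
|---|---|---|---|---|---|---|
| 0.02 | 1.057 | 1.4% | 5.3% | 1.106 | 2.6% | 5.6% |
| 0.05 | 1.143 | 3.4% | 5.8% | 1.266 | 6.3% | 6.5% |
| 0.10 | 1.285 | 6.7% | 6.6% | 1.531 | 12.2% | 8.1% |

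**Step 2: pilot, random routing.** Suppose instead that each of the eight calls goes to a random counsellor, and that a participant's counsellor effect is the average over those calls. Take the total variance as 1 and the counsellor variance as τ² = ICC.

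- The variance of the TSP mean is τ²[1/40 + (39/40)/(154 × 8)] + (1 − τ²)/154. Averaging over calls does not remove the τ²/40 term, because the same 40 counsellors serve the whole arm.
- The variance between participants that an unadjusted model sees falls to (1 − τ²) + τ²(39/40)/8.

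At τ² = 0.05, the true variance of the TSP mean is 0.00746. The unadjusted one is 0.9561/154 = 0.00621. The control contributes 1/146 = 0.00685. The SE ratio is √[(0.00746 + 0.00685) / (0.00621 + 0.00685)] = 1.047. At τ² = 0.10 the same steps give 1.093, and at 0.02 they give 1.019. Simulation gave 1.04 and 1.09 at 0.05 and 0.10. Routing changes the structure but does not make the problem disappear.

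**Step 3: definitive trial.** Plan for 80% power with the ICC taken as zero, equal arms, and 10 clients per counsellor in one arm. True power = Φ(2.80/√[(2 + 9 × ICC)/2] − 1.96).

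- ICC 0.02: Φ(2.80/1.044 − 1.96) = Φ(0.722), about 76%.
- ICC 0.05: Φ(2.80/1.107 − 1.96) = Φ(0.570), about 72%.
- ICC 0.10: Φ(2.80/1.204 − 1.96) = Φ(0.365), about 64%.

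**Step 4: how well the pilot could estimate the ICC.** The large-sample one-way formula is SE = √[2(1 − ICC)²(1 + (m − 1)ICC)² / (m(m − 1)(k − 1))]. With k = 40 and m = 3.75, it gives about 0.076 at ICC 0.05, so an approximate 95% interval of −0.10 to 0.20. The estimate would be rough.

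**The case against.** The strongest reply is that the article is silent rather than wrong. A reader might infer that the model treats all participants as independent. The text does not say so. Generalised structural equation modelling can carry random effects or clustered variances, and such detail is often left to a full protocol or analysis plan, which is not shown. That stands, and it is why the pilot result here is conditional on the model being fitted with nothing beyond what is stated.

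A reader might also infer that TSP outcomes are strictly nested in counsellors, or that the participant–counsellor link has been lost. Neither is supported. Routing to any available counsellor points towards several counsellors per participant, and the article does not say what the platform or the attendance registers record. It can be argued that such mixing dilutes a counsellor effect. Step 2 shows that under random routing the understatement remains of similar size.

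Other points against also stand in part. The affected comparisons are mainly secondary, in a pilot that does not set out to prove superiority, and the effect with even caseloads is small. Participants who never call have no counsellor, which would reduce it further. Staff at the treatment centres could induce some clustering among controls too. The ICC estimate would be too imprecise to separate 0.02 from 0.10. The definitive-trial figures need an assumed caseload and planners who leave clustering out. Even so, a wide interval for the ICC informs that planning better than an unstated zero.

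**Conclusion.** The point holds in a conditional and modest form. The documents establish that 40 lay counsellors deliver treatment in one arm only, that the stated model includes no counsellor effect, and that the variance is the only parameter discussed for the main trial. They do not establish that standard errors will be wrong. That requires a positive ICC and a model fitted as stated.

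In that case, the pilot understatement is about 1% to 7% with even caseloads and up to about 12% at the uneven caseload considered. It would rarely change the reading of a preliminary effect. The stronger reason to act is the pilot's own purpose: without a counsellor ICC, a definitive trial may be sized as if it were zero, with the loss of power shown in step 3. All ICC, CV and future-caseload values are assumptions. This is an improvement that should be made, not a flaw that invalidates the trial.

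**What to change.** 1. State how participants are linked to counsellors. Keep the counsellor identity for each TSP call or, since recruitment has ended, recover it from platform records if they hold it.
2. Fit the generalised structural equation model with a counsellor random effect in the TSP arm only and a separate residual variance in each arm. Where a participant had several counsellors, use multiple-membership weights proportional to sessions delivered. Assigning the participant to the counsellor with most sessions is acceptable only as a stated simplification. Treat controls, and TSP participants with no calls, as singletons.
3. List the counsellor ICC with its interval among the planned pilot outputs, and say that it will be imprecise.

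The cost is one identifier per call, some extra modelling work and slightly wider intervals. Trial status reports only baseline data under analysis, so the outcome model can still be specified. If identities cannot be recovered, say so and show the arm comparison over a range of assumed ICCs.
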